**Figure 1 F1:**
[figure not shown]
Recruitment and randomisation of participants.

This will result in the groups presented in Table 1

**Table 1 T1:** Incentivised and control groups

	**Receiving invitation for 1**^**st **^**time**	**Having received an invitation previously**
Control Group	250 (receiving standard invitation letters; no incentives)	250 (receiving standard invitation letters; no incentives)
Intervention Group	250 (receiving modified invitation letters; incentives)	250 (receiving modified invitation letters; incentives)

## Outcomes

### Uptake

Uptake of each vaccination by participants will be recorded at the community clinics where vaccinations will take place.

### Social deprivation

Levels of social deprivation will be measured by using participants’ postcodes to calculate Index of Multiple Deprivation (IMD) scores. This is a measure of multiple deprivation measured at the small area level, i.e. the Lower Layer Super Output Area (LSOA). It is made up of seven LSOA level domain indices, which relate to income deprivation, employment deprivation, health deprivation and disability, education skills and training deprivation, barriers to housing and services, living environment deprivation, and crime. IMD scores range from 0 to100, with higher scores indicating higher levels of deprivation.

### Informed choice

In order to assess whether the offer of financial incentives undermines the quality of decisions to undertake the HPV vaccinations, a short modified version of a validated measure of informed choice will be used [16]. This will consist of (Additional file 2):

1. Two items rated on a seven point scale, assessing attitudes towards the HPV vaccination: “For me, having the HPV vaccination is (a) 1: not at all good −7: extremely good and (b) 1: not at all harmful-7: extremely harmful.”

2. Three items assessing knowledge of the HPV vaccination by requesting participants to determine the validity (whether true or false) of three statements relating to the vaccination: “If I have the HPV vaccination: I am less likely to get cervical cancer**;** I am less likely to get other sexually transmitted diseases; I am less likely to get pregnant.”

### Sample size determination

According to the latest report from the Department of Health on coverage of the HPV vaccinations [7], the average completion rate for the “catch-up” campaign targeting females aged 17-18 years in the Birmingham East & North Primary Care Trust is 32.4%. Previous studies investigating the impact of financial incentives on uptake of vaccinations have reported an avergage between-group difference of approximately 8.5%: Specifically, Moran et al. [17] reported an effect size of 8.5% for uptake of the influenza vaccination with incentives (20.3% (control group) vs 28.8% (incentivised group)) and Yokley et al. [18] reported an avergage increase of 8.4% in childhood immunisation across three time points with the addition of inventives (at two weeks: 10.1% (control group) vs. 22.5% (incentivised group); at 2 months: 22.7% (control group) vs. 30.8% (incentivised group); at three months: 26% (control group) vs 30.8% (incentivised group)). Based on these figures, we expect financial incentives in this study to increase completion (i.e. uptake of the 3^rd^ vaccination) of the HPV vaccination programme by 8.5%, resulting in a completion rate of 40.9% by incentivised groups. To detect this difference between arms using a two-tailed *χ*^2^ test at the 5% significane level with 80% power, a sample of 1008 participants is required (calculations performed in GPower 3.0); This figure has been rounded off to the nearest whole number, resulting in a required sample of 1000 participants (half of whom consist of previous-non attenders and half of whom, first-time invitees), giving 500 in each intervention arm (See Table 1).

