### Participants

Participants will compromise of 16-18 year old girls, living in Birmingham. To be included in the trial, girls must fulfill the following inclusion criteria:

(a) Live in areas falling under the administration of the Birmingham East and North (BEN) and the Heart of Birmingham Primary Care Trusts

(b) Be registered with a GP within one of the two PCTs

(c) Be eligible to be vaccinated through the clinics (Sutton Cottage, Partners in Health and Dove Medical Centre)

(d) Not have been vaccinated against HPV before.

Half of the sample will consist of girls who have previously received an invitation to get vaccinated, but have failed to attend the first appointment (previous non-attenders). The remaining half will consist of girls who have not yet received an invitation to attend the vaccination programme (first-time invitees).

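### The 80% power rests on a control rate that does not describe the previous non-attenders and on an effect partly averaged over a shrinking gap, and it applies only to the pooled comparison

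*Protocol article*

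**What the plan says.** The section Sample size determination of the protocol article takes one control rate, the average completion "targeting females aged 17-18 years in the Birmingham East & North Primary Care Trust is 32.4" per cent. It adds 8.5 points, "resulting in a completion rate of 40.9% by incentivised groups".

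The effect has two sources:

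- An influenza study that "reported an effect size of 8.5% for uptake of the influenza vaccination with incentives" (20.3% against 28.8%).
- A childhood immunisation study with an average "increase of 8.4% in childhood immunisation across three time points with the addition of inventives". Its last comparison is "at three months: 26% (control group) vs 30.8% (incentivised group").

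The calculation is for a single comparison: "To detect this difference between arms using a two-tailed" chi-squared "test at the 5% significane level with 80% power". It gives 1008, rounded to 1000, or 500 per arm.

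Under Participants, half the sample are "girls who have previously received an invitation to get vaccinated, but have failed to attend the first appointment (previous non-attenders"), and the age range is 16-18. Table 1 puts 250 girls in each arm of each sample. Statistical analysis runs the logistic regressions for first and third doses separately in the two samples. Background places the third dose six months after the first.

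**The concern.** Three inputs or uses of the calculation do not match the trial as described.

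- **Control rate.** A campaign average includes the girls who came when first invited. The previous non-attenders are selected for not having done so, and no rate is given for them. The same paragraph states the half-and-half mix but uses one rate for everyone.
- **Effect.** In the childhood study's printed figures, the incentive arm stays at 30.8% from two to three months while controls rise from 22.7% to 26%. The mean of the three gaps is nearly twice the last gap. The trial's endpoint is a third dose at six months, later than any of them.
- **Unit of analysis.** The 80% is for 500 against 500, but the stated effect analyses are 250 against 250.

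At stake is how a null result is read. A reader who sees 80% would give it more weight than it can bear, above all for a single sample.

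**Working it through.** **Inputs from the protocol.** Control 32.4%, incentive 40.9%, two-sided 5%, 80% power, 500 per arm pooled, 250 per arm in each sample.

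**Formula.** With p̄ = (p1 + p2)/2, a = √[2p̄(1 − p̄)] and b = √[p1(1 − p1) + p2(1 − p2)]:

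- n per arm = (1.960a + 0.842b)² / (p2 − p1)²
- power = Φ{[(p2 − p1)√n − 1.960a] / b}

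**Step 1: reproduce the plan.** For 0.324 and 0.409, a = 0.6814 and b = 0.6788. Then n = 503.3, so 504 per arm and 1008 in total, as stated. At 500 per arm, (1.9007 − 1.3356)/0.6788 = 0.832, which is 79.7% power. Rounding down to 1000 costs almost nothing.

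**Step 2: the childhood study's average.** 22.5 − 10.1 = 12.4; 30.8 − 22.7 = 8.1; 30.8 − 26 = 4.8. The mean is 25.3/3 = 8.43. The average is correct and includes the last time point.

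**Step 3: vary the effect, with control held at 32.4%.** The middle row is the mean of the influenza result and the childhood study's last gap, (8.5 + 4.8)/2 = 6.65.

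| Difference (points) | Power, 500 per arm | Power, 250 per arm | Total N for 80% |
|---|---|---|---|
| 8.5 | 79.7% | 50.5% | 1008 |
| 6.65 | 59.3% | 34.1% | 1628 |
| 4.8 | 35.7% | 20.2% | 3090 |

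**Step 4: vary the non-attenders' control rate.** The documents give no figure, so 10%, 15% and 20% are assumptions. First-time invitees stay at 32.4%, and the blended control rate is the mean of the two. The planned odds ratio is (0.409/0.591)/(0.324/0.676) = 1.444. For example, at a 10% base it gives 13.8% with incentives; the blended rates are then 21.2% and (40.9 + 13.8)/2 ≈ 27.4%, a difference of 6.2 points.

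| Assumed non-attender rate | Blended control | Pooled power, 8.5 points kept | Pooled power, odds ratio 1.44 kept |
|---|---|---|---|
| 10% | 21.2% | 87.1% | 62.3% (6.2 points) |
| 15% | 23.7% | 85.1% | 69.0% (6.9 points) |
| 20% | 26.2% | 83.3% | 73.7% (7.5 points) |

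Power rises or falls according to the scale on which the effect is taken to be constant. The protocol does not discuss the choice.

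**Step 5: the separate analyses.** On the plan's own 32.4% against 40.9% with 250 per arm, (1.3440 − 1.3356)/0.6788 = 0.012, which is 50.5% power. This step needs no outside assumption. For the non-attender sample alone, at assumed rates of 10%, 15% and 20%, power is 78%, 67% and 60% if 8.5 points is kept, and 26%, 34% and 41% if the odds ratio is kept.

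**The case against.** The strongest reply is that nothing has been miscalculated. The 1008 reproduces exactly, the 8.4 average is right, and the influenza study supports 8.5 with no averaging over time. That stands. A reader might infer that the last time point was left out, but it is one of the three values. A reader might also infer that 4.8 is the proper effect. The documents do not support that either: it would discard the influenza result, and three months is itself only a stand-in for six-month completion.

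A second reply is that a lower control rate helps. The plan fixes an absolute difference, and with 8.5 points kept, power rises to 83-87%. The blended rates of 21-26% also lie close to the influenza study's 20.3%. This stands too, so the inference that the general-programme rate must leave the trial below 80% power fails. The reply still needs a premise that the protocol does not state: at a 10% base, 8.5 points means going from 10% to 18.5% among girls who have already failed to attend.

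Third, a combined logistic regression is planned, so a pooled comparison does exist. That is so, but the protocol introduces it to compare the effect between the two samples. The effect of incentives on first and third doses is assigned to the separate models, and the sample size section gives no power for them.

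**Conclusion.** The concern holds in a limited form. The 32.4% does not describe half the trial, and one of the two effect sources averages a gap that had fallen to 4.8 points by three months. The protocol gives no range to show how far the 80% depends on either.

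The size depends on assumptions. Pooled power at 1000 runs from 62% to 87% over assumed non-attender rates of 10-20%, according to whether the odds ratio or the absolute difference is held. From 32.4% it is 59% at 6.65 points and 36% at 4.8. These are scenarios, and none is shown to be the true one. The age difference, 16-18 against 17-18, is a further mismatch whose direction and size cannot be given.

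The firmest figure is the per-sample one. On the plan's own rates, each separate analysis has about 50% power, so the stated 80% can be claimed only for the pooled comparison of 32.4% with 40.9%.

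**What to change.** In Sample size determination:

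- State an assumed control completion rate, or a range such as 10-20%, for previous non-attenders, apart from the rate for first-time invitees. The documents describe no data from earlier re-invitation, so label the range as an assumption.
- Say whether the incentive effect is taken as constant on the absolute or the odds-ratio scale.
- Keep 8.5 points as the planning value if wished, and show 4.8 points as a lower sensitivity scenario, not as the sole effect.
- Restate pooled and per-sample power at 1000 over these assumptions, and say that 80% is for the pooled comparison under 32.4% against 40.9%.

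The cost is one rewritten paragraph and a less favourable stated power. Recruitment, endpoints and the planned models do not change.

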### Evaluation

The evaluation of the financial incentive scheme will be conducted by researchers at King’s College London, Centre for the Study of Incentives in Health (CSI Health, http://www.kcl.ac.uk/csihealth). Data relating to participants’ uptake of each of the three HPV vaccinations, along with their postcodes, age and answers to the measure of informed choice will be transferred by the Healthy Incentives team to CSI Health researchers. All information will be anonymised and kept securely. Data will be transferred via email in password protected files. CSI Health researchers will analyse the data with the aim of: i) determining the impact of financial incentives on uptake of the HPV vaccination and on the quality of girls’ decisions to get vaccinated; and ii) writing up and publishing the findings.

### Statistical analysis

To assess the impact of the intervention on initial uptake (i.e. the 1st vaccination) and completion of the HPV vaccination programme (i.e. the 3rd vaccination) logistic regressions will be performed separately for each of the two samples, i.e. for girls who have not received an invitation to get vaccinated before and those who have received a previous invitation but have failed to attend. To test the moderating effect of social deprivation on the impact of the intervention, the interaction between IMD scores and intervention will be added to the logistic regression models. To test whether there is a difference in the size of effect of the intervention in the two samples, datasets will be combined and another logistic regression conducted, in which whether participants have received an invitation to get vaccinated before or or not will be added as a predictor to the model, along with the intervention. To test for differences in the attrition rates between the 1^st^ and 3^rd^ vaccinations between the invervention and control groups the *χ*^2^ test will be used. Finally, differences in knowledge of the HPV vaccination between intervention and control group will be tested using the *χ*^2^ test, while differences in attitudes towards the HPV vaccination will be examined via a one-way analysis of variance. All tests will be assessed at the 5% level of significance.

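### The stated 80% power belongs to one pooled 500-versus-500 comparison, but uptake is tested in two separate samples of 250 per arm, each with about 50% power at the protocol's planning rates

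*Protocol article*

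**What the plan says.** **Sample size determination.** The planning control rate is an average over the catch-up programme: completion "targeting females aged 17-18 years in the Birmingham East & North Primary Care Trust is 32.4" per cent. Incentives are expected to raise completion by 8.5 percentage points, "resulting in a completion rate of 40.9% by incentivised groups". The calculation is for a single comparison of the two arms by a two-tailed chi-squared test at the 5% "level with 80% power, a sample of 1008 participants is required". This is rounded to 1000 ("half of whom consist of previous-non attenders and half of whom, first-time invitees"), which gives 500 per arm.

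**Trial design and Table 1.** The two samples are described as independent and separately randomised. Each has 250 control and 250 incentive girls.

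**Statistical analysis.** The effect of the intervention on first-dose uptake and on completion, which the Abstract names as the primary outcome, is assessed as follows: "logistic regressions will be performed separately for each of the two samples". A further regression on the combined data has intervention and prior invitation as predictors. Its stated purpose is to see whether the effect differs in size between the samples. Every test is at the 5% level.

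**The concern.** The two sections describe different tests. One is sized on all girls together, while the other judges effectiveness within each half. No analysis that the article assigns to Hypothesis I uses 500 per arm, and no power is given for a single sample.

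The stated power tells the reader how much weight a non-significant result can bear. If it belongs to another test, a null result in one sample looks better supported than it is. At the planning rates, the likeliest pattern under an identical true effect in both samples is one significant and one non-significant result. That pattern could be read as incentives working in only one group.

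There is a related difficulty with the control rate. The 32.4% is a programme average, while half the trial is selected for having missed a first appointment. The article gives no rate for either sample.

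**Working it through.** **Inputs.** From Sample size determination: p1 = 0.324, p2 = 0.409, difference d = 0.085, two-sided alpha 5%, power 80%, total 1008 rounded to 1000. From Table 1: 250 per arm in each sample.

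**Step 1: reproduce the planning figure.** Two proportions, pooled variance under the null, no continuity correction. With p̄ = (0.324 + 0.409)/2 = 0.3665:

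- S0 = √[2p̄(1−p̄)] = 0.6814
- S1 = √[p1(1−p1) + p2(1−p2)] = 0.6788
- n per arm = (1.960·S0 + 0.8416·S1)² / d² = 3.636/0.007225 = 503.3, so 504 per arm and 1008 in total.

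This matches the article and identifies the calculation as one pooled comparison.

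**Step 2: power by number per arm.** Power = Φ[(d√n − 1.960·S0)/S1].

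| n per arm | Argument of Φ | Power |
|---|---|---|
| 504 | 0.844 | 80.1% |
| 500 | 0.832 | 79.7% |
| 250 | 0.012 | 50.5% |

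The non-central chi-squared (50.5%), arcsine (50.6%) and logistic Wald (50.4%) approximations agree at 250 per arm.

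**Step 3: two separate tests at these rates.** The samples are independent, so:

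- both significant: 0.505² ≈ 25%
- exactly one significant: 2 × 0.505 × 0.495 ≈ 50%
- neither significant: 0.495² ≈ 25%.

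From a control rate of 32.4%, 250 per arm reaches 80% power at a difference of about 12.2 points. For 80% power at 8.5 points in each sample, 1008 per sample would be needed, or 2016 in total.

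**Step 4: previous non-attenders at other control rates.** The 5–15% range is an assumption, because the article gives no figure. Two ways of carrying over the planned effect are shown: the same 8.5 points, or the same odds ratio, (0.409/0.591)/(0.324/0.676) = 1.44. The pooled column is the Wald power of a logistic regression stratified by sample, with first-time invitees at 32.4% versus 40.9%. Each sample's log odds ratio is weighted by its information, I = 1/[1/(250·p1(1−p1)) + 1/(250·p2(1−p2))], and power = Φ[(weighted log odds ratio)·√(sum of I) − 1.960].

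| Assumed control rate | Effect carried over | Power in this sample (250 per arm) | Pooled stratified power |
|---|---|---|---|
| 5% | 8.5 points (to 13.5%) | 91% | 90% |
| 10% | 8.5 points (to 18.5%) | 78% | 88% |
| 15% | 8.5 points (to 23.5%) | 67% | 86% |
| 5% | OR 1.44 (to 7.1%) | 16% | 59% |
| 10% | OR 1.44 (to 13.8%) | 26% | 66% |
| 15% | OR 1.44 (to 20.3%) | 34% | 71% |

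Example, 5% with 8.5 points: I = 28.73 and 8.44, log odds ratios 0.367 and 1.087, weighted 0.531. Then 0.531 × √37.17 = 3.24, and Φ(3.24 − 1.96) = 90%.

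**The case against.** **The article never labels a primary analysis, and the combined model will be fitted anyway.** Both statements are correct. Hypothesis I is not split by sample, and the combined model, with intervention and prior invitation as predictors, would yield an overall intervention effect with about 80% power at the planning rates. A reader might infer that the trial cannot test the overall effect at its stated power. The documents do not support that, because the data and the model are both there. What stands is that the article gives this model another purpose, while the sentence on assessing the intervention's effect points to the separate regressions.

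**Separate analysis is legitimate.** Two separately randomised populations may reasonably be analysed apart. The fault lies in pairing that choice with a power statement for something else.

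**The 50% figure is not general.** A reader might infer that a true 8.5-point gain would be missed about half the time in each sample. That requires a control rate near 32.4% in both, which cannot be taken for granted in girls selected for non-attendance. If the absolute gain held there at a control rate of 5–15%, power would be 67–91%. The odds-ratio rows are less favourable, but the article expresses its effect as an absolute difference and never as an odds ratio. Neither set of rows alone shows where the trial stands, so both are given.

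**Misreading of a split result is conjecture.** It is a risk and not a certainty, since a comparison between samples is planned. The mismatch in power does not depend on it.

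**Conclusion.** The stated power is wrong as written for the stated test. The 80% (79.7% at 500 per arm) holds for a pooled comparison that the article does not assign to Hypothesis I. At the protocol's own planning rates, each separate test has about 50% power, both are significant about 25% of the time, and 12.2 points rather than 8.5 are detectable at 80%.

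These figures rest only on 32.4% versus 40.9%, a two-sided 5% level and 250 per arm. For previous non-attenders, the power could be well above or well below 50%, depending on a control rate and an effect scale that the protocol does not give. The same uncertainty affects the pooled test: about 86–90% under a constant 8.5 points and 59–71% under a constant odds ratio, for assumed control rates of 5–15%.

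**What to change.** Reconcile Sample size determination with Statistical analysis. The preferred route is to name one logistic regression on all 1,000 girls, with intervention and prior-invitation status as terms, as the test of Hypothesis I. The by-sample effects are then reported with confidence intervals as secondary estimates. This matches the existing sample size calculation and uses a model already planned. It costs a change of wording in the two sections, with no added participants or data.

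If the separate tests stay as the main analysis, replace the 80% claim with the per-sample power: about 50% at 32.4% versus 40.9%. The 50% and 12.2-point figures apply only at that control rate, so they should not be attached to a sample for which another rate is assumed. Restoring 80% in each sample at the planning rates would need 2016 girls, which is not a wording change.

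Under either route, label the control rate in each sample as an assumption and give a range.

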### Participant recruitment and randomisation

To be included in the study, participants will be selected randomly from a list of names of all girls aged 16-18 years, meeting the above inclusion criteria (See Figure 1). This list will be compiled by the Birmingham Primary Care Shared Services Agency (BPCSSA), which holds and controls all Birmingham patient data, from the names of all 16-18 year old girls eligible to be vaccinated against HPV. The list will be sorted according to whether girls have received a previous invitation to get vaccinated but have failed to attend their first session or have not previously received an invitation. BPCSSA will randomly select 500 participants to be included in the trial from each of these two sub-lists using the RAND() function in Excel. Selected individuals from both the samples will subsequently be separately randomised, via the aforementioned technique, to receive one of two invitations letters:

(a) A standard letter inviting them to attend their first vaccination session (Additional file 1) or

(b) A modified invitation letter, which will include the offer of vouchers worth £45 for receiving the three vaccinations (Additional file 1)

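### The uptake models, as described, do not use IMD or age as baseline covariates; prespecifying both is a small, nearly free gain in efficiency, not the repair of an error

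*Protocol article*

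**What the plan says.** The Statistical analysis section of the protocol article builds the uptake models in steps.

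- First- and third-dose uptake: "logistic regressions will be performed separately for each of the two samples", the samples being first-time invitees and previous non-attenders. No covariate list is given.
- Moderation by deprivation: "the interaction between IMD scores and intervention will be added to the logistic regression models".
- Combined data: prior-invitation status "will be added as a predictor to the model, along with the intervention".

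The combined model therefore has two named predictors, neither of them IMD or age. For the separate models, intervention alone is the natural reading, because IMD is brought in only at the later moderation step.

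The covariates are to hand. Under Social deprivation, the plan is "using participants’ postcodes to calculate Index of Multiple Deprivation (IMD) scores". Under Evaluation, uptake data go to the analysts "along with their postcodes, age and answers to the measure of informed choice". Age also defines the sampling frame, a "list of names of all girls aged 16-18 years" (Participant recruitment and randomisation). On allocation, that section says "Selected individuals from both the samples will subsequently be separately randomised"; neither IMD nor age is a stratification factor.

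**The concern.** Postcode and age are fixed before allocation and exist for girls who never attend as well as for those who do. If they predict uptake, a model that ignores them uses less of the available information than it could.

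This matters more here than in many trials because power is short where the models are fitted. The sample size of 1008, rounded to 1000, is for both samples together, while the uptake models are run within each sample of 500. What is at stake is a few points of power at most, and a slightly tighter risk difference. The validity of the comparison is not in question.

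**Working it through.** **Inputs from the article.** Completion 32.4% (control) and 40.9% (incentive), two-sided 5%, 80% power, 250 per arm in each sample, 500 per arm overall. **Assumed, because the article gives no figure:** log-odds of uptake per SD of 0.2 to 0.6 for IMD and 0.1 to 0.3 for age.

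**1. The plan's own figure.** Pooled-variance formula without continuity correction, with mean rate 0.3665:

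n per arm = [1.960 × √(2 × 0.3665 × 0.6335) + 0.842 × √(0.324 × 0.676 + 0.409 × 0.591)]² / 0.085² = 504 after rounding up, so 1008 in total. The stated figure reproduces exactly. It assumes no covariate adjustment. Power is 79.7% with 500 per arm and 50.5% with 250 per arm.

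**2. Power with and without IMD and age.** Simulated logistic regressions with the marginal rates held at 32.4% and 40.9% (4000 trials at n = 500, 1500 at n = 1000):

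| Log-odds per SD (IMD, age) | n = 500: unadjusted → adjusted | n = 1000: unadjusted → adjusted |
|---|---|---|
| 0.2, 0.1 | 50.8% → 51.6% | 80.6% → 80.9% |
| 0.4, 0.2 | 49.4% → 51.6% | 80.5% → 82.1% |
| 0.6, 0.3 | 50.5% → 54.5% | 80.6% → 84.4% |

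Unadjusted power should be the same down each column. The spread at n = 500 (49.4% to 50.8%) is simulation noise, and it exceeds the 0.8-point gain in the first row. The fair reading is about 0 to 4 points per sample. For the pooled data a separate run put the gain at 0 to 3 points.

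**3. Scale of the estimate.** A further simulation used one covariate, 250 per arm and 3000 trials per scenario:

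| Covariate OR per SD | SE of log OR, unadjusted → adjusted | SD of risk difference, unadjusted → adjusted | Power |
|---|---|---|---|
| 1.25 | 0.187 → 0.189 | 0.0432 → 0.0431 | 51% → 51% |
| 1.5 | 0.187 → 0.191 | 0.0430 → 0.0424 | 51% → 51% |
| 2.0 | 0.187 → 0.197 | 0.0428 → 0.0410 | 49% → 53% |

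The standard error of the log odds ratio rises, because the adjusted odds ratio is conditional and lies further from 1 (mean log odds ratio 0.366 → 0.405 at OR 2.0). On the risk-difference scale the SD falls: by 1.4% at OR 1.5 (0.0006 / 0.0430) and by 4.2% at OR 2.0 (0.0018 / 0.0428). With IMD and age together over the assumed range, the fall is about 0.5% to 4%.

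**4. Chance imbalance.** The standardised IMD difference between arms of 250 has SD √(2/250) = 0.089, so a 95% range of ±1.96 × 0.089 = ±0.175 SD. At log-odds 0.4 this shifts the log odds ratio by ±0.07, which is 19% of the planned effect, ln(1.444) = 0.37. That is a 95% extreme. As a share of sampling variance, IMD imbalance contributes (0.4 × 0.089)² / 0.187² = 0.0013 / 0.035, under 4%, and this is already inside the unadjusted standard error.

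**5. The interaction test.** The text does not say whether an IMD main effect is in the model when the interaction is added. If it were left out, the interaction term would absorb any prognostic effect of IMD. With n = 500, no true interaction and 1000 trials, the false-positive rate was about 12%, 34% and 84% at IMD log-odds of 0.1, 0.2 and 0.4 per SD. With the main effect included it was 5% to 6%.

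**The case against.** The case against has real weight.

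- **The covariate list is not stated either way.** A journal article commonly leaves it to the full protocol or analysis plan. This stands: a reader might infer that the plan excludes covariates, and the article does not say so. It describes models built without them, and the point goes no further than that.
- **The unadjusted analysis is valid.** It matches the χ² basis of the sample size, and the one factor used in randomisation, prior invitation, is respected by separate analysis and by its place in the combined model. This stands in full.
- **Imbalance is not bias.** A reader might infer from the 19% figure that the effect estimate is contaminated. It is not: under randomisation such differences are sampling variation, and the confidence interval allows for them.
- **Adjustment does not shrink the standard error of the odds ratio.** Correct. The benefit shows only in power and on the risk-difference scale.
- **Prognostic strength may be weak.** IMD is an area-level score, age spans only 16 to 18, and Hypothesis II treats deprivation as a moderator of the incentive's effect, not as a predictor of uptake. This is why the range starts near zero.

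A reader might also infer that the test of Hypothesis II is invalid for want of an IMD main effect. The article is silent on that term, and many analysts would include it by default, so only an ambiguity worth closing can be claimed.

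What survives is that the covariates are at hand, no scenario showed a material loss of power, and the change costs almost nothing.

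**Conclusion.** A minor improvement, not an error. As described, the uptake models leave out IMD and age, which the analysts will hold. Including them would add about 0 to 4 points of power per sample, from about 50%, and make the SD of the risk difference about 0.5% to 4% smaller. These sizes rest entirely on the assumed prognostic strengths. Near the lower end the gain cannot be told apart from simulation noise. Adjustment does not restore the 80% power that the pooled calculation aims at: even the strongest assumption leaves each sample at about 54.5%.

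**What to change.** In the Statistical analysis section, or in the analysis plan:

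1. Prespecify continuous IMD and age as main effects in the first- and third-dose models for each sample, and in the combined model, which already holds the prior-invitation indicator.
2. Report a risk difference standardised over all randomised girls beside the odds ratio, and label the odds ratio as conditional.
3. Keep the unadjusted model as a sensitivity analysis.
4. State that the IMD-by-intervention term is tested with the IMD main effect in the model.

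The cost is a few sentences and no new data collection. One thing to confirm: the Procedure section lists addresses but not age among the details passed on for every invited girl, so the transfer should draw age from the selection list and cover non-attenders too. The downsides are that the adjusted odds ratio is conditional, hence the standardised risk difference, and that the gain may prove negligible.
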